**Methods::**

This study will be a randomized intervention, parallel, multicenter study in collaboration with 45 urological outpatient clinics at the national level. Patients will be assigned in a 1:1 ratio to the experimental and control groups using simple randomization according to odd and even numbers assigned sequentially to the patients at each clinic. The experimental intervention will be 12 weeks. The experimental group will receive oral treatment with duloxetine at a daily dose of 2 × 40 mg and will be required to perform innovative PFMT. The control group will receive the same oral duloxetine treatment (2 × 40 mg a day) but will not perform PMFT. Data will be collected from both groups before intervention and after the 12-week intervention is completed.

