### Exclusion criteria

2.5

1.Recent use of any pharmacologic agent to treat symptoms of urinary incontinence in the past 6 months;2.History of anti-incontinence surgery in the past 12 months;3.Use of onabotulinum toxin A for the treatment of urinary incontinence in the past 12 months;4.History of pelvic prolapse repair or urethral surgery in the past 12 months;5.History of PFMT in the past 12 months;6.History of interstitial cystitis or bladder-related pain;7.Chronic severe constipation;8.Clinically significant renal or hepatic impairment;9.Clinically significant heart impairment;10.Women who are pregnant, lactating or actively trying to become pregnant;11.Non-compliance with limitation of duloxetine treatment for mixed urinary incontinence;12.Positive urinary tract infection;13.Use of rehabilitation aids (pessary, urethral plugs, vaginal beads, et cetera);14.Use of antidepressant(s);15.Insufficient understanding of pelvic floor exercises and/or omitting exercises;16.Participation in any clinical study in the past 6 months.

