#### Experimental group

2.6.2

PFMT with stabilizing exercises (Table 2)

1.Oral administration of treatment with duloxetine at a daily dose of 2 × 40 mg for 12 weeks.2.PFMT with lumbopelvic stabilization will be performed.3.PFMT exercises will be performed 5 times a week for 20 to 30 minutes a day, after initial training with a physiotherapist.a.Educating probands about anatomy, physiology and pelvic floor muscle functions;b.Training pelvic floor muscles in different positions;c.Training pelvic floor muscles with lumbopelvic stabilization.

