### Adherence

2.8

Eligibility, cooperation and security will be recorded during recruitment and study implementation. The lead researcher, in collaboration with urologists, will register appropriate patients from all databases in outpatient registries. The number of suitable patients from the total patients considered will be recorded. During the intervention period, collaboration and adherence as well as treatment discontinuation will be recorded. Adherence to medication dosage and exercise treatment specifications will be required.

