## Discussion

3

The study protocol presents the starting points and design of a randomized-intervention, multicenter study with the aim of evaluating the effect of the combination duloxetine and PFMT therapy versus duloxetine treatment alone in women with SUI. The study may provide evidence of the efficacy of combined treatment for SUI and indicate an active approach for the treatment of SUI through exercise.

The strength of the study is it promotes an innovative, non-invasive and conservative treatment of strengthening pelvic floor muscles with stabilization exercises in addition to duloxetine treatment. We will use 3 standardized measuring tools: ICIQ-UI SF, OAB-q-short version and I-QoL. Both groups will receive daily oral 80 mg duloxetine (2 × 40 mg), and an innovative PFMT will be added in the experimental group. Interventions will last for 12 weeks, and will consist of exercise 5 times a week for 30 minutes. Education of probands regarding anatomy, physiology, and pelvic floor muscles—so that they properly understand the impact of exercises—will be done by a physiotherapist in collaboration with a nurse 5 times. Subsequently, exercises will be performed at home, and a diary control will be used to ensure compliance.

Based on similar studies, we expect good patient adherence, a low level of patient dropout and agreement with the study protocol. Patients who will be assigned to a duloxetine-only group will be offered the opportunity to exercise after of the 12-week treatment. We expect a 20% subject dropout. The success of our treatment will be a decline of more than 50% in the difficulties associated with SUI symptoms.

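### Exclusion item 15 counts omitting exercises, which in practice can happen only after randomisation and only in the PFMT arm, so applying it could bias the comparison

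*Protocol article*

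**What the plan says.** All references are to the protocol article.

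- **Section 2.5, item 15** excludes women for "Insufficient understanding of pelvic floor exercises and/or omitting exercises".
- **Section 2.5, item 5** separately excludes "History of PFMT in the past 12 months".
- **Section 2.6.2** gives the exercise programme to the experimental group only: "PFMT exercises will be performed 5 times a week for 20 to 30 minutes a day, after initial training with a physiotherapist".
- **Abstract, Methods** says that the control group takes the same duloxetine "but will not perform PMFT". The Discussion adds: "Patients who will be assigned to a duloxetine-only group will be offered the opportunity to exercise after of the 12-week treatment".
- **Discussion**, on the experimental programme: "exercises will be performed at home, and a diary control will be used to ensure compliance".
- **Section 2.8** says that adherence and treatment discontinuation are recorded during the intervention period, and then: "Adherence to medication dosage and exercise treatment specifications will be required".
- **Section 2.6.1, item 6**, which covers both groups, has patients return after 12 weeks of full treatment for the questionnaire and adverse-effect report. It makes no exception for women who did not adhere.
- **Section 2.9** names a general linear model and a mixed-design ANOVA. It does not say who is included.

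**The concern.** Eligibility criteria should be settled before allocation, on information available in the same way for both arms. Half of item 15 does not meet that standard. A woman can omit exercises only once exercises have been assigned to her, and here that happens after randomisation and in one arm.

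If an investigator applies the item to a randomised woman whose diary shows missed sessions, she leaves the PFMT arm. The equally unmotivated woman in the control arm has no exercises to miss and stays. The arms are then no longer comparable by randomisation. If motivation is related to outcome, a difference can appear with no effect of PFMT at all. If PFMT does work, removing the women who did not do it also removes dilution of its effect.

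The trial's hypothesis is that adding PFMT is superior, so a bias in that direction would matter. Outcomes are collected only before and after the intervention. A woman who is removed in between and not followed up has no 12-week value, and no later analysis can restore it.

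**Working it through.** **Step 1: when and in whom can the criterion be met?**

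| Moment | Control arm | PFMT arm |
|---|---|---|
| Screening | No trial exercises assigned; PFMT in the past 12 months already excluded | Same |
| During the 12 weeks | No PFMT | Programme 5 times a week at home, with a diary |
| After the 12 weeks | Exercise offered | Programme completed |

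The only cell in which omission can occur and be seen while the trial comparison is running is the PFMT arm during treatment. No run-in or exercise test before allocation is described. Understanding of the exercises is different: it could be judged at screening in every candidate.

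**Step 2: the plan's own numbers.** Section 2.3 gives power 0.80, alpha 0.05, 63 per group, 20% loss and at least 158 in total. With a standardised difference of 0.5 (my assumption; the article states none) and a two-sided test:

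n = 2 × (1.960 + 0.842)² / 0.5² = 62.8, so 63 per group.

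126 / (1 − 0.20) = 157.5, so 158 in total, or 79 per arm.

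**Step 3: illustration of the bias.** The assumptions, none of them from the documents, are:

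- PFMT has no true effect.
- A fraction f = 0.20 of the PFMT arm is removed and not analysed.
- The removed women's outcomes are g = 0.5 to 1.0 SD worse than those of the women retained.
- Nobody else is lost.

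If the retained mean is m, the full-arm mean is (1 − f)m + f(m − g) = m − fg. The spurious difference is therefore fg:

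- g = 0.5: 0.20 × 0.5 = 0.10 SD
- g = 1.0: 0.20 × 1.0 = 0.20 SD

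I start from 79 per arm because 63 is already net of the planned loss; removing 20% from 63 would count that loss twice. The PFMT arm becomes 79 × 0.80 = 63.2, so 63, against 79 controls. The standard error is √(1/79 + 1/63) = 0.169 SD. With two time points, the group-by-time test is a two-sample t test on the change.

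- Bias 0.10 SD: 0.10 / 0.169 = 0.59 standard errors, false-positive rate about 9%
- Bias 0.20 SD: 0.20 / 0.169 = 1.18 standard errors, false-positive rate about 22%

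**Step 4: sensitivity to the assumptions.** A second model removes the least adherent fraction q from the PFMT arm, where adherence has correlation ρ with outcome. The bias is ρ × φ(z_q) / (1 − q), again with 79 randomised per arm.

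| q | ρ | Bias (SD) | False-positive rate |
|---|---|---|---|
| 5% | 0.1 | 0.01 | 5.1% |
| 20% | 0.1 | 0.035 | 5.5% |
| 20% | 0.3 | 0.105 | 9.6% |
| 20% | 0.5 | 0.175 | 18.7% |
| 30% | 0.5 | 0.25 | 31% |
| any | 0 | 0 | 5% |

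With negative ρ the bias reverses. The result therefore runs from negligible to serious, depending on two quantities that the documents do not give.

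**The case against.** A good deal can be said on the other side.

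- **Understanding can be tested at screening.** This stands. Only the part of item 15 on omitting exercises is tied to the period after allocation.
- **The item may mean unwillingness, or a programme dropped more than 12 months ago.** Item 5 does not reach that far back, so the text does not strictly rule this out. It is a strained reading, though, because inclusion item 7 already asks for willingness to accept randomisation and take part fully in tests. If it is what was meant, the wording still needs correcting.
- **Nothing says that these women are dropped.** This stands, and it limits the point. A reader might infer that the primary analysis will compare adherent PFMT users with all controls. No section says so: section 2.6.1, item 6 calls patients back without exception, and section 2.9 defines no analysis population. The statistical analysis plan is not shown and may keep these women.
- **Section 2.8 might be read as ordering removal.** It does not. It has adherence recorded, and the requirement that follows carries no sanction and covers medication in both arms. Likewise, the diary in the Discussion is there so that "a diary control will be used to ensure compliance"; it is not linked to exclusion.
- **The size is assumed.** This stands. The 20% in section 2.3 is overall loss, not removal for omitted exercise, and the Discussion expects good adherence. Nor do the documents establish that the bias favours PFMT; that needs poorer adherers to have worse outcomes.

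What these arguments leave untouched is the criterion itself. It is a stated rule, not a detail left to another document, and it can act on one arm only.

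**Conclusion.** The concern holds in a conditional form. As worded, the part of item 15 on omitting exercises can in practice be met only after randomisation and only in the PFMT arm. If it is applied and the women concerned leave follow-up or analysis, the randomised comparison is broken on one side and could be biased. A bias in favour of PFMT is plausible, but only if poor adherers have worse outcomes.

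The documents support no figure for its size. The 0.10 to 0.20 SD, with a false-positive rate of about 9% to 22%, illustrates 20% one-sided removal with outcomes 0.5 to 1.0 SD worse. If 0.5 SD is the difference behind the sample size, this is 20% to 40% of it (0.10 / 0.5 and 0.20 / 0.5). Weaker assumptions bring the bias close to zero.

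It would be wrong to say that the trial's result is biased, or that non-adherers will be left out of the primary analysis. The text permits that outcome and does not state it. The correction is still worth making before it can matter, because 12-week outcomes that were not collected cannot be recovered.

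**What to change.** 1. **Section 2.5, item 15:** delete the part on omitting exercises. Either have understanding of the exercises judged in all candidates before allocation, or delete that part as well.
2. **Section 2.6.1 or 2.9:** state that every randomised woman is asked to complete the 12-week questionnaires whatever her adherence, and is analysed in the arm to which she was allocated. Results in adherent women only are supplementary.
3. **Section 2.8:** keep the recording of adherence and the existing requirement. Add one sentence saying that non-adherence does not lead to exclusion from follow-up or analysis.

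The cost is a wording change. Once every randomised woman is followed up and kept in her arm, this criterion contributes no selection bias. The planned total of 158 is unchanged. The one drawback is that the estimated effect may be somewhat smaller, because women who did not exercise remain in the PFMT arm.

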### Interventions

2.6

#### Experimental and control groups

2.6.1

1.Oral administration of daily duloxetine (2 × 40 mg) for 12 weeks.2.During the screening period, the usual procedure for the indication of duloxetine treatment will be used.3.Questionnaires will be completed before initiation of duloxetine titration treatment.4.After a 2-week titration, full treatment in both arms of the study will commence.5.After 2 weeks of titration treatment, the full dose will be administered. This dose administration will continue until the end of the 12-week treatment for both control and experimental groups.6.After 12 weeks of full treatment, patients will be required to visit researchers, and they will complete a questionnaire and report adverse effects.7.At study completion, patients may continue treatment at the discretion of the treating physician.

#### Experimental group

2.6.2

PFMT with stabilizing exercises (Table 2)

1.Oral administration of treatment with duloxetine at a daily dose of 2 × 40 mg for 12 weeks.2.PFMT with lumbopelvic stabilization will be performed.3.PFMT exercises will be performed 5 times a week for 20 to 30 minutes a day, after initial training with a physiotherapist.a.Educating probands about anatomy, physiology and pelvic floor muscle functions;b.Training pelvic floor muscles in different positions;c.Training pelvic floor muscles with lumbopelvic stabilization.

**Table 2 T2:**
[figure not shown]
Pelvic floor muscle training exercise protocol.

### Outcome measures

2.7

#### Primary measurements

2.7.1

Urine leakage symptoms will be reported according to an assessment from the International Consultation on Incontinence Questionnaire Urinary Incontinence Short Form (ICIQ-UI SF), which was developed by the International Continence Society (ICS). It monitors the frequency and amount of escaped urine in the first 2 questions. The third question assesses how much the urine leakage interferes with the patient's daily life. The ICIQ-UI SF score is the sum of questions: 0 = no leakage, 21 = very severe urine leakage).^[15]^ Cronbach's alpha for the ICIQ-UI SF is 0.95.^[16]^

Symptoms will also be reported using the Overactive Bladder Questionnaire (OAB-q). This questionnaire about urge urinary incontinence symptoms focusses on the symptoms of urge incontinence that occur in the 4 weeks before evaluation. It contains 6 questions with symptom scores that range from 0 (none) 100 (maximum) symptoms and 13 questions that assess quality of life. A score of 100 corresponds to the best quality of life and 0 the worst.^[17,18]^ Cronbach's alpha for the OAB-q is 0.90.^[19]^

#### Secondary measurements

2.7.2

##### Change in quality of life according to I-QoL

2.7.2.1

I-QoL is a self-assessment scale for evaluating the quality of life of urinary incontinence patients. It is divided into three subscales: avoidance and limiting behavior, psychosocial impact and social embarrassment. It contains 22 questions (0 = worst quality of life, 100 = best quality of life). Cronbach's alpha for the I-QoL is 0.91 to 0.96.^[20–22]^

##### PGI-I score

2.7.2.2

The PGI evaluates the status of urination problems compared to the condition before a patient started treatment in the study. Patient impressions are evaluated according to the following scores: 1 = much better; 2 = quite better; 3 = a little better; 4 = no change; 5 = a little worse; 6 = a lot worse; 7 = definitely worse.^[23]^

Comparison of the combined duloxetine and PFMT therapy to duloxetine treatment alone will be evaluated according to efficacy and side effects.

#### Adverse events - harms

2.7.3

The adverse events in connection with duloxetine use will be investigated. These effects include nausea, fatigue, insomnia, dry mouth, constipation, impaired consciousness, dizziness, headache, diarrhea, double vision depression, and abdominal pain.

### Adherence

2.8

Eligibility, cooperation and security will be recorded during recruitment and study implementation. The lead researcher, in collaboration with urologists, will register appropriate patients from all databases in outpatient registries. The number of suitable patients from the total patients considered will be recorded. During the intervention period, collaboration and adherence as well as treatment discontinuation will be recorded. Adherence to medication dosage and exercise treatment specifications will be required.

### Data analysis

2.9

Descriptive and inference statistics will be used to analyze the data. Unpaired *t* tests will be used to compare the experimental and control groups before training. We expect that our data will be normally distributed. Differences between the control and experimental groups before and after the intervention will be evaluated with a general linear model (GLM) and mixed design analysis of variance (ANOVA) using repeated measurements with the Greenhouse-Geisser correction. The significance level will be set at 95%, and *P* < .05 will be considered significant. Effect size (ES) will be calculated based on partial eta squared (η^2^). According to Cohen,^[24]^ the small, medium and large ANOVA effect sizes (η^2^) will be classified as: 0.00 to 0.003, no effect; 0.010 to 0.039, small; 0.060 to 0.110, medium; 0.140 to 0.200, big. Calculations will be made in IBM SPSS 22 Windows (IBM, Chicago, IL).

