### Sample size

2.3

We used power analysis to determine an appropriate sample size; the test strength was set at 0.80 and alpha at 0.05 (type I error). An estimated 63 probands are required for each group (experimental and control). We anticipate a 20% loss in participation and will therefore include a total of at least 158 probands. Based on sample selection, we expect a decrease in incidence after intervention from 10% to 35%. A decrease of more than 50% will be considered a success.

Listed below are the inclusion and exclusion criteria for the DULOXING trial.

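### As written, the two-time-point ANOVA with a final visit tied to finishing treatment leads to a complete-case analysis, about 126 of 158 women on the plan's own allowance

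*Protocol article*

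**What the plan says.** All references are to the protocol article.

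- **Data analysis (2.9)** compares the arms before and after the intervention with a "general linear model (GLM) and mixed design analysis of variance (ANOVA) using repeated measurements with the Greenhouse-Geisser correction", run in SPSS.
- **Abstract, Methods** gives two data collections: one before the intervention and one once the 12-week intervention is complete.
- **Experimental and control groups (2.6.1)** words the final assessment as "After 12 weeks of full treatment, patients will be required to visit researchers", where the questionnaire is completed and adverse effects are reported.
- **Sample size (2.3)** requires 63 women per group and continues: "We anticipate a 20% loss in participation and will therefore include a total of at least 158 probands". The Discussion repeats the allowance: "We expect a 20% subject dropout".
- **Adherence (2.8)** states that "collaboration and adherence as well as treatment discontinuation will be recorded". It does not say whether outcomes are still collected after a woman stops.
- **Exclusion criteria (2.5), item 15** lists poor understanding of the exercises or omitting them. It does not say whether this applies only at entry or also later.
- **Experimental group (2.6.2)** prescribes exercise five times a week for 20 to 30 minutes. The control arm has no exercise programme.

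**The concern.** A repeated-measures ANOVA on two time points needs both values from each woman. If the second value is sought only after a full course of treatment, women who stop early are the ones most likely to lack it. The named procedure then leaves them out unless another step is specified.

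Women who stop are seldom a random subset. In this trial a reason to stop may exist in one arm only, because the exercise programme is in one arm only. Exclusion item 15 adds to this. Omitting exercises can be seen only once exercise has begun, so if the item were applied after randomisation it could remove women from the combined arm and never from the control arm. The comparison would then be between selected groups, not the groups formed by randomisation.

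A larger intake does not help with this, because it narrows the confidence interval around whatever quantity the complete cases estimate.

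**Working it through.** **1. The plan's own figure.** Inputs from Sample size (2.3): 63 per group, 20% loss.

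63 / (1 − 0.20) = 78.75, rounded up to 79 per arm; 2 × 79 = 158. The stated total is reproduced. The analysed number is then 2 × 63 = 126, and 158 − 126 = 32 women are allowed for as lost.

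**2. What the named model does.** With two time points, the group-by-time test is the unpaired t test on change scores, so a woman without a final value contributes nothing to it. The Greenhouse-Geisser factor lies between 1/(k − 1) and 1 for k time points. With k = 2 both limits equal 1, so the correction changes nothing.

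**3. Bias formula.** Let pE and pC be the proportions lost in the exercise and control arms. Let gE and gC be how much worse, in SD, the lost women fare than the completers of their arm. In each arm the all-randomised mean is the completer mean minus p × g. So:

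bias of the complete-case difference = pE × gE − pC × gC.

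Equal rates and equal gaps give zero. Equal rates with different gaps do not: at 20% in both arms, with gaps of 1.0 and 0.5 SD, the bias is 0.20 × 1.0 − 0.20 × 0.5 = 0.10 SD.

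**4. Range under assumptions.** The article gives neither the split of losses by arm nor the gap, so both are assumed here, with gE = gC = g. The type I error is the two-sided 5% rejection rate when there is no true effect among all 79 + 79 randomised women, with standard error √(1/nE + 1/nC) and n = 79 × (1 − p) in each arm. The last column starts from a completer difference of 0.50 SD. That value is also an assumption: it gives 63 per group by the normal approximation (64 with the t distribution), but the article does not state it.

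| Loss, exercise/control | g (SD) | Bias (SD) | Type I error | 0.50 SD in completers becomes |
|---|---|---|---|---|
| 20%/20% | any | 0 | 5.0% | 0.50 |
| 25%/15% | 0.25 | 0.025 | 5.2% | 0.475 |
| 25%/15% | 0.5 | 0.05 | 5.9% | 0.45 |
| 25%/15% | 1.0 | 0.10 | 8.7% | 0.40 |
| 30%/10% | 0.25 | 0.05 | 5.9% | 0.45 |
| 30%/10% | 0.5 | 0.10 | 8.6% | 0.40 |
| 30%/10% | 1.0 | 0.20 | 20.0% | 0.30 |

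Worked row (30%/10%, g = 1.0): bias = 0.30 − 0.10 = 0.20; nE = 55.3, nC = 71.1; standard error = 0.179; bias / standard error = 1.12; rejection rate 20.0%.

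If the larger loss is in the control arm, each bias keeps its size and changes sign. The two-sided error rate is the same, and the complete-case analysis understates the combined arm.

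**5. ANCOVA against change scores.** The change-score comparison fixes the coefficient of baseline at 1, whereas ANCOVA estimates it. With equal variances at both times and correlation ρ, the variance ratio of ANCOVA to change score is (1 − ρ²) / [2(1 − ρ)] = (1 + ρ)/2, which never exceeds 1.

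**The case against.** The strongest reply is that the article never restricts the analysis to completers. It names a model, but no analysis population, and it does not rule out imputation before the ANOVA. The sentence on the final visit describes the normal course and exempts nobody. The evaluation plan in Table 1 is not visible. Analysis sets and missing-data rules commonly sit in a full protocol or SAP, which are not shown. All of this stands. A reader might infer that the plan declares a completers-only analysis, or that women who stop have no scheduled outcome, but the text supports neither. The point is limited to where the stated method and the stated timing lead if nothing is added.

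Three further replies also stand:

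- Inflating for 20% loss is ordinary practice and fits an as-randomised analysis equally well. Loss to participation is not the same as stopping duloxetine or exercise. The 32 women are a planning allowance, not a forecast, and the Discussion also expects little dropout.
- A reader might infer that the analysis flatters the combined arm. That needs more, or worse-faring, losses in that arm. Duloxetine side effects fall on both arms, and control women may leave because they are given no exercise, so the sign could be the reverse.
- ANCOVA by itself also drops a woman with no final value. Protection against bias comes from continued follow-up and from imputation, and ANCOVA adds precision.

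The reply does not remove the two stated elements, which are an outcome assessment worded as following completed treatment and a model that needs both values. An analysis plan can add imputation, but it cannot recover questionnaires that were never collected.

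**Conclusion.** The point holds in a limited form. Followed as written, the plan leads to a complete-case analysis, of about 126 of 158 women if the 20% allowance is used up. The only stated provision for loss is a larger intake, which serves power and not validity. Differential loss is plausible from the design, because one arm alone exercises and exclusion item 15 could act in that arm alone, but the documents do not establish it.

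The bias cannot be computed from the article. The range of 0.025 to 0.20 SD, with type I error of 5.2% to 20.0%, rests on assumed loss splits and assumed gaps between lost women and completers. It can have either sign, and it is zero if losses are equal in rate and reason. The inert Greenhouse-Geisser correction does no harm, but it shows that the stated model does not suit a design with one baseline and one follow-up.

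**What to change.** 1. **Timing of the final assessment (Abstract, Methods; 2.6.1).** Define it by time since start for every randomised woman, whether or not she still takes duloxetine or exercises. Name the day from which time is counted, since 2.6.1 includes a titration period. The outcomes are self-report questionnaires, so post or telephone will serve where a visit fails. State that item 15 of 2.5 does not remove randomised women from follow-up or analysis.
2. **Model (2.9).** Replace the repeated-measures ANOVA and its Greenhouse-Geisser correction by ANCOVA of the week-12 score on arm and baseline, with women analysed as randomised. The baseline is already collected.
3. **Missing values.** Impute remaining missing week-12 scores by multiple imputation using arm, baseline and the adherence and discontinuation data already recorded under 2.8. Add a sensitivity analysis that varies the missing outcomes in both arms, not only in the combined arm.

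The cost is revised wording, a few extra posted or telephoned questionnaires, and possibly a smaller estimated effect. The first item must be settled while women can still be reached; the other two can be settled before the data are analysed.
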